## 11. MEASUREMENT OF EFFECT

Although response is not the primary endpoint of this trial, patients with measurable disease will be assessed by standard criteria. For the purposes of this study, patients should be re-evaluated every 8 weeks. In addition to a baseline scan, confirmatory scans will also be obtained 4 weeks following initial documentation of an objective response.

### 11.1 Antitumor Effect – Solid Tumors

For the purposes of this study, patients should be re-evaluated for response every 2 cycles (approximately 8 weeks). In addition to a baseline scan, confirmatory scans should also be obtained 4 (not less than 4) weeks following initial documentation of objective response.

Response and progression will be evaluated in this study using the new international criteria proposed by the revised Response Evaluation Criteria in Solid Tumors (RECIST) guideline (version 1.1). Changes in the largest diameter (unidimensional measurement) of the tumor lesions and the shortest diameter in the case of malignant lymph nodes are used in the RECIST criteria.

#### 11.1.1 Definitions

Evaluable for toxicity. All patients will be evaluable for toxicity from the time of their first treatment with trametinib.

Evaluable for objective response. Only those patients who have measurable disease present at baseline, have received at least one cycle of therapy, and have had their disease re-evaluated will be considered evaluable for response. These patients will have their response classified according to the definitions stated below. (Note: Patients who exhibit objective disease progression prior to the end of cycle 1 will also be considered evaluable.)

Evaluable Non-Target Disease Response. Patients who have lesions present at baseline that are evaluable but do not meet the definitions of measurable disease, have received at least one cycle of therapy, and have had their disease re-evaluated will be considered evaluable for non-target disease. The response assessment is based on the presence, absence, or unequivocal progression of the lesions.

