| * See RECIST 1.1 manuscript for further details on what is evidence of a new lesion.                                                                                                                                                                                                                                                            |                             |             |                  |                                                      |
| ** Only for non-randomized trials with response as primary endpoint.                                                                                                                                                                                                                                                                            |                             |             |                  |                                                      |
| *** In exceptional circumstances, unequivocal progression in non-target lesions may be accepted as disease progression.                                                                                                                                                                                                                         |                             |             |                  |                                                      |
| Note: Patients with a global deterioration of health status requiring discontinuation of treatment without objective evidence of disease progression at that time should be reported as “ symptomatic deterioration. ” Every effort should be made to document the objective progression even after discontinuation of treatment. |                             |             |                  |                                                      |

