- At least 12 patients (1 per participating institution) will be entered into Group A (normal liver function). Patients in Group A are included in this study to obtain PK data in the same manner as for the patients with liver dysfunction. This group will also be followed for toxicity, but the definitions of recommended dose that are specific to patients with liver dysfunction will not be used.
- If a delay in completing one cohort occurs (*e.g.* severe liver dysfunction cohort has been completed enrollment), study data analysis and reporting will be considered for cohorts that have been completed. The enrollment for the remaining cohorts will continue concomitantly to data analysis.
- Toxicity will be graded according to the NCI CTCAE v4.0.0 and relationship to the study drug; results will be tabulated by liver dysfunction group. All patients who receive any amount of trametinib will be evaluable for toxicity, but patients who receive other than the prescribed dose and do not experience a DLT will be considered inevaluable for DLT. Patients who are not evaluable for DLT will be replaced. One exception is made for patients enrolled in the severe hepatic dysfunction cohort (Group D). As patients with severe hepatic dysfunction can deteriorate quickly due to their disease and poor organ functions, patients in this cohort who complete PK schedule at day 16 will be considered evaluable for DLT assessment.

Primary Endpoints:

- To provide appropriate dosing recommendations for patients with varying degree of hepatic dysfunction receiving trametinib (mild, moderate and severe).
- To establish the maximum tolerated dose (MTD) and dose-limiting toxicity (DLT) of trametinib in advanced cancer patients with varying degrees of hepatic dysfunction
- To characterize the PK profile of trametinib in advanced cancer patients with varying degrees of hepatic dysfunction.

Secondary Endpoints:

- To document the non-DLTs associated with the administration of trametinib in patients with varying degrees of hepatic dysfunction.
- To document any antitumor activity associated with trametinib treatment of patients enrolled on this study.
- To explore and characterize predictive biomarkers for individual cancer patients utilizing genomic sequencing technologies.

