### 13.2 Sample Size/Accrual Rate

- A total of 12 patients will be accrued in the Normal Hepatic Function cohort. A minimum of 3 and a maximum of 12 patients will be accrued in the Mild Hepatic Dysfunction cohort (B). A minimum of 6 and a maximum of 22 patients will be accrued in the Moderate Hepatic Dysfunction cohort (C). A minimum of 6 and a maximum of 22 patients will be accrued in the Severe Hepatic Dysfunction cohort (D). In total this study will accrue a minimum of 27 and a maximum of 68 patients.

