### 13.4 Analysis of Secondary Endpoints

Summary statistics, such as the mean, median, counts and proportion, will be used to describe patients' clinical characteristics. Objective response to treatment will be assessed using the RECIST criteria 1.1. If no objective responses are observed in a disease-specific dose expansion cohort with a minimum of 10 patients evaluable for response, there is  $\geq 89\%$  probability to exclude a true objective response rate of  $\geq 20\%$ .

Predictors of clinical outcomes will be investigated using logistic regression, Cox proportional hazards regression and/or generalized estimating equations as appropriate. Potential predictors include clinical predictors and molecular correlates. Descriptive statistics and plotting of data will also be used to better understand potential relationships.

Frequency and severity of adverse events will be tabulated using counts and proportions detailing frequently occurring, serious and severe events of interest. Adverse events will be summarized using all adverse events experienced, although a sub-analysis may be conducted including only those adverse events in which the treating physician deems possibly, probably or definitely attributable to one or both study treatments. Attempts to model associations between pharmacokinetic data with toxicity profiles will be performed primarily using descriptive statistics; however, logistic regression may be used if warranted.

All analyses will be considered exploratory and inference will be performed with appropriate caution. For all statistical tests, two-sided tests will be performed and no p-value adjustment performed due to the exploratory nature of these tests. A p-value of 0.05 or less will be considered statistically significant.

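### The response-evaluable set drops treated patients who stop without re-evaluation, so any non-zero response rate computed on it is biased upward

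*Protocol*

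**What the plan says.** Section 11.1.1 of the protocol admits to the objective-response set only patients with measurable disease at baseline who "have received at least one cycle of therapy, and have had their disease re-evaluated will be considered evaluable for response". A note in the same paragraph adds one exception: "Patients who exhibit objective disease progression prior to the end of cycle 1 will also be considered evaluable". By contrast, the toxicity set in that section includes every patient from the first dose.

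Section 11.1 plans re-evaluation every two cycles, so the first planned scan falls at about 8 weeks. The note under Table 25 covers decline without a scan: "Patients with a global deterioration of health status requiring discontinuation of treatment without objective evidence of disease progression at that time should be reported". The label it gives them is symptomatic deterioration. The note also asks sites to try to document progression after treatment stops, but no rule counts such patients as non-responders.

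Section 13.1 makes an allowance for Group D in the DLT set. The reason given is this: "As patients with severe hepatic dysfunction can deteriorate quickly due to their disease and poor organ functions". The allowance itself reads: "patients in this cohort who complete PK schedule at day 16 will be considered evaluable for DLT assessment". There is no matching allowance for response.

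Section 13.4 contains the only response calculation. It concerns a disease-specific expansion cohort "with a minimum of 10 patients evaluable for response" in which no response is seen. Section 1.2 lists antitumour activity as a secondary objective for the patients enrolled, and Section 11 says that response is not the primary endpoint.

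**The concern.** Both added conditions, a completed cycle and a repeat assessment, are events after baseline, and failing to meet them is often itself a treatment failure. A patient who was never re-evaluated has no documented response. Removing that patient shrinks the denominator and leaves the numerator unchanged.

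The exception for early progression is narrow. It needs objective progression within the first 28 days, whereas the first planned scan is at about 8 weeks, so it normally depends on an unscheduled scan.

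The definition also fits poorly with the rest of the protocol. The objective in Section 1.2 covers enrolled patients, not those who stayed long enough to be re-scanned. Harm is counted on everyone treated and benefit on a selected subset. Section 3.1.1 admits tumour types with very limited expected activity to the moderate and severe cohorts under a separate consent form, and Section 13.1 allows completed cohorts to be reported separately. An overstated response rate would be unhelpful in that setting.

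**Working it through.** **1. The plan's own figure.** Section 13.4 states at least 89% probability of excluding a true response rate of 20% or more after no responses in 10 evaluable patients.

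- 1 − 0.8^10 = 0.8926, which reproduces the statement.
- If three leavers were added as non-responders: 1 − 0.8^13 = 0.945.
- The estimate is 0% on either denominator, so this statement is not inflated. Counting leavers would only strengthen it.

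**2. Who is dropped.** Applying Section 11.1.1 to treated patients with measurable disease who leave before the first planned scan:

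| Situation | In the response set? |
|---|---|
| Objective progression documented before the end of cycle 1 | Yes |
| One cycle received, treatment stopped, then re-scanned | Yes |
| One cycle received, never re-scanned | No |
| Less than one cycle, no objective progression documented | No |

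The last two rows hold patients who stop for toxicity, decline, withdrawal or death.

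**3. Size of the bias.** Let N be the treated patients with measurable disease, R the responders, and d the share dropped, none of whom has a documented response.

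Evaluable rate ÷ all-treated rate = [R / (N(1 − d))] ÷ (R / N) = 1/(1 − d).

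If a share L leaves before re-evaluation and a share k of these leavers is kept in the set, then d = L(1 − k). The documents give neither L nor k, so both are assumptions.

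| L (assumed) | k = 0 | k = 0.5 | k = 1 |
|---|---|---|---|
| 10% | 1.11 | 1.05 | 1.00 |
| 20% | 1.25 | 1.11 | 1.00 |
| 30% | 1.43 | 1.18 | 1.00 |
| 40% | 1.67 | 1.25 | 1.00 |
| 50% | 2.00 | 1.33 | 1.00 |

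**4. Illustration.** Section 13.2 sets Group D at 6 to 22 patients. Take 22, all assumed to have measurable disease, with an assumed 2 responders. The all-treated rate is 2/22 = 9.1%.

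- 4 dropped: 2/18 = 11.1%
- 7 dropped: 2/15 = 13.3%
- 11 dropped: 2/11 = 18.2%

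**The case against.** The strongest reply is that little depends on this rate, and that the protocol limits the loss.

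- **Role of response.** It is secondary, and Section 13.4 calls all its analyses exploratory. Dose decisions rest on DLT and PK. This stands and limits the consequence.
- **Provisions that keep patients in.** The study calendar (Table 24) appears to place a lesion assessment at follow-up, and the note under Table 25 presses for documentation of progression after discontinuation. A patient who had one cycle, stopped and was then scanned counts as re-evaluated, so staying on treatment to week 8 is not required. This also stands, and is why the table above has columns for k above zero. It does not help patients who die or are too ill to be scanned, or those with less than one cycle and no documented progression.
- **Left to the analysis plan.** An all-treated line could appear in a statistical analysis plan that is not shown, and Section 11.1.1 does not forbid one. But the evaluable set itself is fixed in the protocol, so the bias on that set is open to comment here.

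A reader might infer more than the documents support:

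- **That the protocol compares response between hepatic groups and will overstate benefit in severe impairment.** The objective in Section 1.2 is not broken down by hepatic group, and Section 13.4 plans no such rate or comparison. The groups would differ on any denominator, because Section 3.1.1 admits certain low-activity tumour types only to the moderate and severe cohorts.
- **That the inflation is known to be largest in Group D.** Section 13.1 says these patients can decline quickly, and Section 2.1 describes hepatic-dysfunction patients as generally unstable. That makes it plausible, but no loss rate is given for any group.
- **That the zero-in-ten statement is inflated.** Step 1 shows that it is not.

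**Conclusion.** The point holds as a modest, directional bias in a secondary, exploratory outcome. The set in Section 11.1.1 excludes treated patients who stop without re-evaluation unless objective progression was documented before the end of cycle 1. Any non-zero response rate on it is therefore too high as a description of treated patients.

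For an assumed 20% to 50% leaving early, the factor is 1.25 to 2.0 if none are kept and 1.11 to 1.33 if half are. If all are kept there is no inflation. These figures assume that no dropped patient responded, which is true by construction for anyone never re-evaluated. The loss rates are assumptions throughout. The bias is probably greatest in the hepatic-dysfunction cohorts, Group D in particular. The dosing recommendations, which rest on DLT and PK, are unaffected.

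**What to change.** In Sections 11.1.1 and 13.4, define the main objective response rate on all treated patients with measurable disease at baseline, and count those never re-evaluated as non-responders. This matches the objective in Section 1.2. Keep the present evaluable set as a supplementary figure, and state how many patients it leaves out and why, so that the actual loss is visible.

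The cost is one revised definition, one extra table line and a slightly less favourable response rate. No new data, visits or patients are needed, and no treatment rule changes.

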#### 11.1.2 Disease Parameters

Measurable disease. Measurable lesions are defined as those that can be accurately measured in at least one dimension (longest diameter to be recorded) as  $\geq 20$  mm by chest x-ray or as  $\geq 10$  mm with CT scan, MRI, or calipers by clinical exam. All tumor measurements must be recorded in millimeters (or decimal fractions of centimeters).

Note: Tumor lesions that are situated in a previously irradiated area might or might not be considered measurable. *If the investigator thinks it appropriate to include them, the conditions under which such lesions should be considered must be defined in the protocol.*

**Malignant lymph nodes.** To be considered pathologically enlarged and measurable, a lymph node must be  $\geq 15$  mm in short axis when assessed by CT scan (CT scan slice thickness recommended to be no greater than 5 mm). At baseline and in follow-up, only the short axis will be measured and followed.

**Non-measurable disease.** All other lesions (or sites of disease), including small lesions (longest diameter  $< 10$  mm or pathological lymph nodes with  $\geq 10$  to  $< 15$  mm short axis), are considered non-measurable disease. Bone lesions, leptomeningeal disease, ascites, pleural/pericardial effusions, lymphangitis cutis/pulmonitis, inflammatory breast disease, and abdominal masses (not followed by CT or MRI), are considered as non-measurable.

Note: Cystic lesions that meet the criteria for radiographically defined simple cysts should not be considered as malignant lesions (neither measurable nor non-measurable) since they are, by definition, simple cysts.

‘Cystic lesions’ thought to represent cystic metastases can be considered as measurable lesions, if they meet the definition of measurability described above. However, if non-cystic lesions are present in the same patient, these are preferred for selection as target lesions.

**Target lesions.** All measurable lesions up to a maximum of 2 lesions per organ and 5 lesions in total, representative of all involved organs, should be identified as **target lesions** and recorded and measured at baseline. Target lesions should be selected on the basis of their size (lesions with the longest diameter), be representative of all involved organs, but in addition should be those that lend themselves to reproducible repeated measurements. It may be the case that, on occasion, the largest lesion does not lend itself to reproducible measurement in which circumstance the next largest lesion, which can be measured reproducibly should be selected. A sum of the diameters (longest for non-nodal lesions, short axis for nodal lesions) for all target lesions will be calculated and reported as the baseline sum diameters. If lymph nodes are to be included in the sum, then only the short axis is added into the sum. The baseline sum diameters will be used as reference to further characterize any objective tumor regression in the measurable dimension of the disease.

**Non-target lesions.** All other lesions (or sites of disease) including any measurable lesions over and above the 5 target lesions should be identified as **non-target lesions** and should also be recorded at baseline. Measurements of these lesions are not required, but the presence, absence, or in rare cases unequivocal progression of each should be noted throughout follow-up.

### 11.1.3 Methods for Evaluation of Measurable Disease

All measurements should be taken and recorded in metric notation using a ruler or calipers. All baseline evaluations should be performed as closely as possible to the beginning of treatment and never more than 4 weeks before the beginning of the treatment.

The same method of assessment and the same technique should be used to characterize each identified and reported lesion at baseline and during follow-up. Imaging-based evaluation is preferred to evaluation by clinical examination unless the lesion(s) being followed cannot be imaged but are assessable by clinical exam.

Clinical lesions: Clinical lesions will only be considered measurable when they are superficial (*e.g.*, skin nodules and palpable lymph nodes) and  $\geq 10$  mm diameter as assessed using calipers (*e.g.*, skin nodules). In the case of skin lesions, documentation by color photography, including a ruler to estimate the size of the lesion, is recommended.

Chest x-ray: Lesions on chest x-ray are acceptable as measurable lesions when they are clearly defined and surrounded by aerated lung. However, CT is preferable.

Conventional CT and MRI: This guideline has defined measurability of lesions on CT scan based on the assumption that CT slice thickness is 5 mm or less. If CT scans have slice thickness greater than 5 mm, the minimum size for a measurable lesion should be twice the slice thickness. MRI is also acceptable in certain situations (*e.g.* for body scans).

Use of MRI remains a complex issue. MRI has excellent contrast, spatial, and temporal resolution; however, there are many image acquisition variables involved in MRI, which greatly impact image quality, lesion conspicuity, and measurement. Furthermore, the availability of MRI is variable globally. As with CT, if an MRI is performed, the technical specifications of the scanning sequences used should be optimized for the evaluation of the type and site of disease. Furthermore, as with CT, the modality used at follow-up should be the same as was used at baseline and the lesions should be measured/assessed on the same pulse sequence. It is beyond the scope of the RECIST guidelines to prescribe specific MRI pulse sequence parameters for all scanners, body parts, and diseases. Ideally, the same type of scanner should be used and the image acquisition protocol should be followed as closely as possible to prior scans. Body scans should be performed with breath-hold scanning techniques, if possible.

PET-CT: At present, the low dose or attenuation correction CT portion of a combined PET-CT is not always of optimal diagnostic CT quality for use with RECIST measurements. However, if the site can document that the CT performed as part of a PET-CT is of identical diagnostic quality to a diagnostic CT (with IV and oral contrast), then the CT portion of the PET-CT can be used for RECIST measurements and can be used interchangeably with conventional CT in accurately measuring cancer lesions over time. Note, however, that the PET portion of the CT introduces additional data, which may bias an investigator if it is not routinely or serially performed.

Ultrasound: Ultrasound is not useful in assessment of lesion size and should not be used as a method of measurement. Ultrasound examinations cannot be reproduced in their entirety for independent review at a later date and, because they are operator dependent, it cannot be guaranteed that the same technique and measurements will be taken from one assessment to the next. If new lesions are identified by ultrasound in the course of the study, confirmation by CT or MRI is advised. If there is concern about radiation exposure at CT,

MRI may be used instead of CT in selected instances.

Endoscopy, Laparoscopy: The utilization of these techniques for objective tumor evaluation is not advised. However, such techniques may be useful to confirm complete pathological response when biopsies are obtained or to determine relapse in trials where recurrence following complete response (CR) or surgical resection is an endpoint.

Tumor markers: Tumor markers alone cannot be used to assess response. If markers are initially above the upper normal limit, they must normalize for a patient to be considered in complete clinical response. Specific guidelines for both CA-125 response (in recurrent ovarian cancer) and PSA response (in recurrent prostate cancer) have been published. In addition, the Gynecologic Cancer Intergroup has developed CA-125 progression criteria which are to be integrated with objective tumor assessment for use in first-line trials in ovarian cancer.

Cytology, Histology: These techniques can be used to differentiate between partial responses (PR) and complete responses (CR) in rare cases (*e.g.*, residual lesions in tumor types, such as germ cell tumors, where known residual benign tumors can remain).

The cytological confirmation of the neoplastic origin of any effusion that appears or worsens during treatment when the measurable tumor has met criteria for response or stable disease is mandatory to differentiate between response or stable disease (an effusion may be a side effect of the treatment) and progressive disease.

FDG-PET: While FDG-PET response assessments need additional study, it is sometimes reasonable to incorporate the use of FDG-PET scanning to complement CT scanning in assessment of progression (particularly possible 'new' disease). New lesions on the basis of FDG-PET imaging can be identified according to the following algorithm:

- a. Negative FDG-PET at baseline, with a positive FDG-PET at follow-up is a sign of PD based on a new lesion.
- b. No FDG-PET at baseline and a positive FDG-PET at follow-up: If the positive FDG-PET at follow-up corresponds to a new site of disease confirmed by CT, this is PD. If the positive FDG-PET at follow-up is not confirmed as a new site of disease on CT, additional follow-up CT scans are needed to determine if there is truly progression occurring at that site (if so, the date of PD will be the date of the initial abnormal FDG-PET scan). If the positive FDG-PET at follow-up corresponds to a pre-existing site of disease on CT that is not progressing on the basis of the anatomic images, this is not PD.
- c. FDG-PET may be used to upgrade a response to a CR in a manner similar to a biopsy in cases where a residual radiographic abnormality is thought to represent fibrosis or scarring. The use of FDG-PET in this circumstance should be prospectively described in the protocol and supported by disease-specific medical literature for the indication. However, it must be acknowledged that both approaches may lead to false positive CR due to limitations of FDG-PET and biopsy resolution/sensitivity.

Note: A 'positive' FDG-PET scan lesion means one which is FDG avid with an uptake

greater than twice that of the surrounding tissue on the attenuation corrected image.

